## Abstract

**Background:**

Leprosy leads to nerve damage and slow-healing ulcers, which are treatable with routine therapy. There has been a recent resurgence of interest in the use of honey for the treatment of different kinds of wounds.

**Objective:**

The aim of this study, Honey Experiment on Leprosy Ulcer (HELP), is to evaluate the healing properties of raw, unadulterated African honey in comparison with normal saline dressing for the treatment leprosy ulcers.

**Methods:**

This is a multicenter, comparative, prospective, single-blinded, parallel-group, and 1:1 individually randomized controlled trial to be conducted at The Leprosy Referral Hospital, Chanchaga in Minna, Niger State, North Central Nigeria, and St. Benedict Tuberculosis and Leprosy Rehabilitation Hospital in Ogoja, Cross River State, South-South Nigeria. Raw, unadulterated honey will be used in the ulcer dressing of eligible, consenting participants in the intervention group, whereas those in the control group will be treated by dressing with normal saline. The main outcomes will be the proportion of complete healing and the rate of healing up to 84 days after randomization. Follow-up will be conducted 6 months after randomization. We aim to enroll 90‐130 participants into the study. Blinded observers will examine photographs of ulcers to determine the outcomes.

**Results:**

The recruitment of trial participants began on March 14, 2022, and has been continuing for approximately 24 months.

**Conclusions:**

Our study will provide an unbiased estimate of the effect of honey on the healing of neuropathic ulcers.

## Introduction

### Background and Rationale

Leprosy or Hansen disease is a chronic granulomatous disease caused by *Mycobacterium leprae* [1]. The disease morbidity is characterized by damage to the skin and peripheral nerves, causing neuropathy and severe disability and consequently resulting in social exclusion and stigmatization [2]. Leprosy is preventable and treatable with multidrug therapy but remains endemic in many communities of people living in poverty and with poor hygiene [2]. Nigeria reported a total of 1417 new cases of leprosy in 2020, including 87 new child cases [3], with a grade-2 disability rate of about 15% for the past 5 consecutive years [4].

A total of 30% to 50% of people infected with leprosy globally are reported to eventually have nerve damage or neuropathy [5]. Ulcers usually occur in anesthetic feet and will heal slowly with routine therapy; however, they have a tendency to recur [6].

The use of honey as a therapeutic agent in the treatment of wounds dates back to ancient times, with the earliest documented report being recorded in the *Edwin Smith Papyrus* (2600‐2200 BCE) [7]. Honey is a viscous, supersaturated solution containing sugars, water, amino acids, vitamins, minerals, enzymes, and many other substances that is derived from nectar gathered and modified by the honeybee, *Apis mellifera* [8,9]. Studies have suggested that honey promotes wound healing, stimulates tissue growth, facilitates debridement and epithelization, deodorizes, reduces edema and exudates, and possesses antimicrobial properties [7,10,11].

There has been a recent resurgence of interest in the use of honey for the treatment of different kinds of wounds, as researchers continue to search for improved, cost-effective, and readily available agents to promote wound healing [9,12]. Although there is a sizeable number of reports that show mixed levels of effectiveness in the use of honey as a topical agent for the treatment of different types of ulcers, our search of numerous databases revealed a paucity of documentation on the use of honey in the treatment of ulcers in leprosy. The effectiveness of honey to promote the healing of ulcers in general remains uncertain. A Cochrane review has reported several studies with unclear outcomes for trials with honey on venous leg ulcers, diabetic foot ulcers, and mixed chronic wounds [9]. Most of the reported studies were adjudged by the reviewers to be of low quality due to imprecision and high risk of bias. The review suggested the high risk of bias in the reports were due to nonblinding of study participants and health care professionals. Statistical heterogeneity was evident across studies [9].

The current practice for the dressing of leprosy ulcers in Nigeria is the use of normal saline [13]. Honey is acknowledged to be safe for use in wound dressings [14], with only about 5% of patients reporting pain following dressing. There is also an undocumented concern of botulism disease due to infection with *Clostridium botulinum* [15] that is associated with the use of honey, as it is considered a suitable environment for the anaerobic bacteria to thrive. This study will evaluate the effectiveness of honey in the treatment of ulcers in leprosy in comparison with normal saline dressing.

### Objectives

The aim of this study, Honey Experiment on Leprosy Ulcer (HELP), is to evaluate the healing properties of raw, unadulterated African honey in comparison with normal saline dressing for the treatment of leprosy ulcers.

The study objectives are as follows:

Recruit 90‐130 eligible, consenting people within 12 months.Randomize the participants to receive ulcer dressing with either honey (intervention group) or normal saline (control group) twice a week.Observe the rate of healing based on 2 observations per week (cm^2^ per unit time, until either the ulcer has healed or 84 d have elapsed since randomization).Observe the time to healing, defined as complete re-epithelization (up to a maximum of 84 d).Monitor the rate of activity of study participants with pedometers.Monitor the recurrence of treated ulcers or appearance of new ulcers and any anatomical changes in the limb at 6-month follow-up after randomization.

### Trial Design

The study is a multicenter, prospective, single-blinded, parallel group, and 1:1 individually randomized controlled trial. The study duration is 48 months (maximum), with recruitment starting at month 5 and postdischarge follow-up starting at month 11. We aim to enroll between 90 and 130 participants over a 24-month recruitment period. The study pathway is shown in Figure 1.

**Figure 1. F1:**
[figure not shown]
Honey Experiment on Leprosy Ulcer (HELP) study pathway.

## Methods

### Study Setting

The study centers are The Leprosy Referral Hospital, Chanchaga in Minna, Niger State, North Central Nigeria, and St. Benedict Tuberculosis and Rehabilitation Hospital in Ogoja, Cross River State, South-South Nigeria. The main study will be preceded by prestudy due diligence.

The Leprosy Referral Hospital, Chanchaga in Minna, Nigeria, is a specialist hospital operated by the government of Niger State in collaboration with The Leprosy Mission (TLM) Nigeria. The hospital was established in 1940 and has 2 wards (eye and physiotherapy units), a theater, a laboratory, and a dispensary. The hospital is supported by an orthopedic workshop that is built and managed by TLM Nigeria, which produces assistive devices including wheelchairs, crutches, protective sandals, and artificial legs.

St. Benedict Tuberculosis and Rehabilitation Hospital is a tuberculosis and leprosy referral hospital located in Ogoja, a town in the northern part of Cross River State of Nigeria. It is owned by the Catholic Diocese of Ogoja, Cross River State, Nigeria. It provides these services in collaboration with the National Tuberculosis and Leprosy Control Programme and with the technical assistance of German Leprosy and TB Relief Association. The center has a community outreach program, which covers 31 communities in the Bekwarra, Ogoja, and Yala local government areas of Cross River State.

### Ethical Considerations

The trial will be conducted in full conformance with the principles of the Declaration of Helsinki and Good Clinical Practice Guidelines. It will also comply with all applicable UK legislation and standard operating procedures for University of Birmingham–sponsored studies. Ethics approval has been granted in Nigeria for the study by the National Health Research Ethics Committee (approval FHREC/2022/01/09/04-02-22) and Niger State Ministry of Health (reference STA/495/Vol/199).

### Eligibility Criteria

The local, medically qualified researchers employed on the grant will screen all ulcer admissions. The researchers will complete web-based eligibility forms for each patient with an ulcer. Consent will be sought by the research fellow from consecutive patients aged ≥18 years with a foot or leg ulcer between 2 and 20 cm^2^ and not requiring surgery (eg, skin graft). The inclusion criteria are as follows:

Patients with a chronic foot ulcer of at least 6-week duration due to leprosy neuropathy.Patients ≥18 years of age.Ulcer with a surface area between 2 and 20 cm^2^ inclusive.Ulcer is clean, dry, and free from infection.Patient can provide informed consent.

The exclusion criteria are as follows:

Any significant medical condition, laboratory abnormality, or psychiatric illness that would prevent the participants from participating in the study.Ulcers with a surface area <2 or >20 cm^2^.Patient requires a skin graft.Any condition that confounds the ability to interpret data from the study (ie, patients with HIV or tuberculosis under active treatment).Any wound that has clinical microbial infections.Diabetes or diabetic ulcer.A patient has returned to the hospital having already taken part in the trial.

The wound dressing protocol for the HELP study is shown in Multimedia Appendix 1.

In the uncommon scenario where a participant has more than 1 foot ulcer, the largest ulcer will be selected as the index ulcer before randomization, and all ulcers will receive the same treatment (eg, if the participant is in the intervention group, all ulcers—not just the 1 being monitored for the trial—will be treated with honey). Observations will be made on all ulcers, but only the largest ulcer will be used in the primary analysis (see the *Discussion* section). Eligible patients will be offered entry in the trial at the point where their senior clinician judges them to be suitable for the honey treatment. This point arises once the lesion has been cleared of any debris or infection, typically by 7‐10 days after beginning treatment with or without antibiotic or debridement.

Swabs of the ulcer area will be taken to assess the wound for bacterial infections prior to the recruitment of participants into the study.

### Informed Consent Collection

Researchers at the study center have been trained on Good Clinical Practice. They will be responsible for the screening of eligible participants and taking of consent. The participant information sheet has been translated into the local language (Hausa). All relevant information for the research participants on the study are contained in the participant information sheet. The information sheet will be given to the participants a day before enrollment into the study. The content of the information sheet will be explained to them verbally, and they will be encouraged to ask questions should they need more clarification. Written informed consent will be sought from the eligible participants after the study has been explained to them and they have taken time to decide to enroll into the study. The consent form will be signed or thumb- or fingerprinted by the participants before enrollment.

### Additional Consent Provisions for the Collection and Use of Participant Data and Biological Specimens

The participant information sheet contains all information about the data to be collected and how the data will be stored and used. Biological specimens such as a swab of the ulcer surface will be obtained for the purpose of screening for bacterial infections prior to the recruitment of a participant into the study. Participants who refuse to give consent will continue to receive normal care from the hospital, but they will not be part of the study.

Participants can decide to withdraw their consent at any time during the study. Such participants will be given a form to complete, stating their reason for withdrawal. A participant may either withdraw fully or they may withdraw from treatment but consent to ongoing data collection.

Once a person consented to participate in the trial, baseline data will be collected. This will precede randomization.

Data will be collected directly onto electronic tablets, and the computer program (Research Electronic Data Capture [REDCap]; Vanderbilt University) will check the range of the information. Photographs of the ulcers will be captured using the tablet device. Each participant will be allocated a unique trial number, which will be included in all data entry forms and linked to the photographs. The level of activity (step count) will be recorded at each dressing change across both intervention and control groups until 84 days or discharge, whichever comes first. This date will enable us to check for postrandomization (“performance”) bias.

### Interventions

#### Explanation for the Choice of Comparators

The participants in the control group will receive the usual care of twice weekly normal saline dressings only. Normal saline dressing is the standard ulcer dressing method currently in use in the hospitals where the trial is taking place.

#### Intervention Description

The intervention for this study is raw, unadulterated honey obtained from local bee farmers in North Central Nigeria. The honey samples have been examined at The National Institute for Pharmaceutical Research and Development, Abuja, and confirmed to be free from microbial contaminants. The honey is stored in airtight plastic containers at room temperature and away from direct sunlight. The honey will be applied topically to the wound during dressing under strict hygienic conditions by using sterilized equipment.

The treatment will be applied at twice weekly dressing changes by local trained nurses or paramedics. These dressing changes are part of routine care and will thus be applied to the intervention and control groups. Dressing changes may take slightly longer for participants in the intervention group, but pain is unlikely as the affected limb has a loss of sensation. Participants in both groups have twice weekly dressing changes during their hospital stay until the ulcers are healed. Any missed sessions will be noted, but this will not be treated as a protocol deviation.

#### Interval Pilot to Monitor the Blinding of Observations

We are concerned that honey residue may be discernible by the observers of the ulcer outcome. We will therefore conduct an interval pilot to examine this issue. To ensure proper blinding of the trial, images of the ulcers from the second dressing change (following the honey or saline application at the first dressing change) for the first 10 enrolled participants will be sent to 3 independent assessors in Nepal. The assessors will look out for traces of honey residues that might interfere with blind assessment during the study. If the assessors are able to distinguish between cases treated with honey and controls, then we will consider alternating honey and saline dressings and making weekly observations rather than twice weekly observations.

We will also make a video recording of the first dressing change for the first 5 intervention and 2 control participants and send it to the 3 independent assessors. An uninterrupted video recording will be made from before the dressing is removed until after it has been replaced.

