### Assignment of Interventions: Blinding

#### Researcher Blinding

Only the overall on-site research supervisor, the database managers at the University of Birmingham and the University of Ibadan Trials Unit, the clinical staff carrying out dressing changes in the room designated for this purpose, and the participants themselves will be aware of the participants’ randomly assigned group. Ward staff will not be informed. The assessors in Nepal will be blinded from the treatment provided for the randomly assigned groups.

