### Data Collection and Management

#### Plans for the Assessment and Collection of Outcomes

Standardized photographs [20] will be taken twice weekly of the dressing changes during the in-patient stay for participants in both intervention and control groups. Any residual honey will be gently removed with a wet swab. Photographs will be taken using the built-in camera in the tablet devices (Samsung Galaxy Tab S7, 13Mp). The photographs will be taken perpendicular to the ulcer. For calibration purposes, a 3-cm clean paper ruler with the date and participant’s trial identification number will be placed in the photograph frame above or below the ulcer but at the level of the skin. The photographs will then be uploaded onto the REDCap database platform and accessed by database managers at the University of Birmingham. The ulcer photos will then be randomized and sent to the blinded assessors in Nepal for the measurement of ulcer dimensions. The photographs will be evaluated digitally by the designated observer in Nepal using the PictZar Digital Planimetry Software with the electronic PUSH Tool (National Pressure Injury Advisory Panel [21]). The observer will delineate an area of interest by manually “painting” the ulcer area with color using a computer mouse. The software will then calculate the ulcer dimensions based on this profile.

The assessors will be blinded to the treatment allocated to the participant. The assessors are all experienced in leprosy, ulcer care, and the measurement of ulcers using the PictZar software. All photographs from a given participant will be assigned to the observers at random. To ensure that the measurements are not all relegated to the end of the study, they will be made in batches of 10 participants—when they reach the completion of their treatments. A proportion (20/100, 20%) of all ulcer photographs will be measured by 2 assessors to estimate interrater reliability. These photographs will be selected at random.

Treatment will stop when the local clinician determines that complete epithelization has taken place. Photographs will be taken at this point and at the follow-up visit.

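### Unmasked videos of product application for 7 participants go to Nepal assessors whom the protocol calls blinded, which also undercuts the residue pilot

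*Protocol article*

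**What the plan says.** The section on the interval pilot describes two streams of material. Still images from the second dressing change of the first 10 enrolled "will be sent to 3 independent assessors in Nepal", who look for honey residue that could undo blind assessment. Those images are placed at the second change because they come "following the honey or saline application at the first dressing change". The section then adds: "We will also make a video recording of the first dressing change for the first 5 intervention and 2 control participants". The film has the same recipients as the still images, since it is to go to the three assessors already named. On the span of the film it says: "An uninterrupted video recording will be made from before the dressing is removed until after it has been replaced".

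The Intervention Description states when the product goes on: "The honey will be applied topically to the wound during dressing".

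The Researcher Blinding section gives a closed list of those who know the allocation: the overall on-site research supervisor, the database managers at two universities, the staff who change the dressings, and the participants. It then says: "The assessors in Nepal will be blinded from the treatment provided for the randomly assigned groups". The section on assessment and collection of outcomes says: "The ulcer photos will then be randomized and sent to the blinded assessors in Nepal for the measurement of ulcer dimensions".

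**The concern.** Dressing staff and participants know the arm, and the Concealment Mechanism section says that it is revealed to the local clinician. Ulcer area comes from an outline that an observer paints by hand, which involves judgement. Blinded reading of photographs is therefore the trial's main protection against detection bias, and the pilot exists to test that protection. A step in the pilot that shows the treatment to assessors described as blinded works against its own purpose.

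Two things are at stake. The first is the pilot's answer. If the assessors can tell honey from saline, the protocol will consider a different dressing pattern and less frequent observation, so a contaminated answer could prompt a change for the wrong reason. The second, which depends on who reads the outcome photographs, is the measured ulcer area of the filmed participants.

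**Working it through.** The protocol states no figure on this point, so the check sets the sections side by side. The only arithmetic is the share of participants affected.

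**1. Does the film show the allocation?** It runs without a break from before removal to after replacement. Honey is applied during dressing, and the pilot section places the first honey or saline application at the first dressing change, which is the one filmed. The application is therefore on film. Nothing says that this part is cut or masked.

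**2. Who sees it?** The film goes to the three independent assessors, and the definite article points back to the three in Nepal who receive the still images. Researcher Blinding leaves assessors in Nepal off its list of those who know the allocation and calls them blinded without qualification. The two sections conflict as written. A separate pilot panel in Nepal would still contradict the blanket statement.

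**3. Can the film inform on residue?** At the first change the dressing coming off predates any trial product, so no residue of trial honey is expected. The second-change images do fit the residue question.

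**4. How far do the filmed participants overlap with the pilot images?** Let h be the number allocated to honey among the first 10 enrolled. The number of filmed participants among those 10 is min(5, h) + min(2, 10 − h).
- h = 5: 5 + 2 = 7, all of them.
- h = 4: 4 + 2 = 6.
- h = 3: 3 + 2 = 5.
- h = 6, 7 or 8: 5 + 2 = 7.

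With 1:1 allocation in permuted blocks, h should be near 5. So the three assessors would probably be asked whether they can tell honey from saline on images of which 5 to 7 in 10 come from participants whose treatment they have been shown.

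**5. Share of the trial.** Filmed: 5 + 2 = 7.
- Of planned enrolment: 7/130 = 5.4%; 7/90 = 7.8%.
- Of the honey arm (65 or 45 at 1:1): 5/65 = 7.7%; 5/45 = 11.1%.
- Of the saline arm: 2/65 = 3.1%; 2/45 = 4.4%.
- Of the interim set of 49, if all seven are in it, as early enrolment makes likely: 7/49 = 14.3%.

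**6. Could a reader link a photograph to a film?** Photographs are put in random order before they are sent. Each frame, however, carries a ruler with the date and the trial identification number. If the photograph is taken during the filmed change, the film may show that number beside the treatment. Otherwise the link depends on recognising the ulcer.

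**The case against.** The strongest reply is that the document never says the three pilot assessors also measure outcomes. It speaks variously of independent assessors, blinded assessors and a designated observer. This is a condensed article, and the full protocol may separate the roles. That stands: outcome bias is conditional on an unstated overlap, and a separate panel would largely remove it. It would not remove the conflict with Researcher Blinding or the damage to the pilot.

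The film's own purpose is not stated either, so it may serve another use, such as showing dressing and cleaning technique. That also stands, but no such use requires assessors who must stay blinded to see the product applied. Nor does the protocol fix the order of viewing. If the still images were judged before the films were seen, the residue test would survive; but each film is made one visit before the corresponding image, and nothing prevents it from being seen first.

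A reader might infer that the films teach assessors what a honey-treated ulcer looks like and so unblind the whole trial. The documents do not support this. At the first change the ulcer has had no trial honey until it is applied and covered, and outcome photographs are taken at later changes after residue has been wiped away with a wet swab.

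A reader might also count up to 7 × 24 = 168 compromised images (two a week for 84/7 = 12 weeks). That is a ceiling. It needs all seven to stay in hospital unhealed for 84 days, whereas the protocol expects at least 70% to heal by then under standard care.

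**Conclusion.** The point holds as an internal contradiction with a limited reach. Followed as written, the pilot discloses the allocation of 7 participants (5.4% to 7.8% of planned enrolment) to assessors whom the protocol elsewhere calls blinded. It also weakens the residue test on the first 10 enrolled. The second conclusion assumes that most filmed participants are among those 10, and that the films are seen before the images are judged.

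Detection bias in the trial's results is a conditional risk. It requires that the pilot assessors also measure outcome photographs and can link a photograph to a film. The exposed quantity is then assessor-measured ulcer area, and so the rate of healing, in these 7 participants. Time to healing is less exposed to the extent that it follows the local clinician's judgement of complete epithelization, which ends treatment. No size of bias can be derived from the document, and none is claimed.

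**What to change.** - Do not send footage of product application to anyone who reads pilot or outcome images. Restrict it to people already on the Researcher Blinding list, such as the on-site research supervisor. The Trial Management Group is not on that list, so passing the films to it would widen the unblinding.
- If footage is needed to judge residue, film the second or a later change and end the clip after cleaning, before any product is applied.
- State in the pilot, Researcher Blinding and outcome assessment sections whether the pilot assessors measure outcomes, so that the three agree.
- Recruitment began in March 2022, so the first participants have probably been filmed already. If the films were sent, assign those participants' photographs to an existing assessor who has not seen them, where one is available. Report the main outcomes, above all the rate of healing, with and without these 7 participants.

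The cost is a few sentences of protocol text, a different cut point for any further film, some reassignment of photographs, and one sensitivity analysis. No added patients or staff are needed.
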